### Primary outcome

The primary outcome is length of hospital stay from the time of admission until discharge, with comparison of the groups.

### Secondary outcomes

The secondary outcomes are readmission and mortality measured as time to event within 3 and 6 months from discharge, with comparisons between the groups. Total lean mass, total fat mass, total fat-free mass, leg lean mass, and trunk fat mass measured as mean changes from admission to discharge and from discharge to 3 months after discharge, with comparisons between groups. Health-related quality of life and activities of daily living measured as mean change from admission to discharge and from discharge to 3 months after discharge, with comparisons between groups. Muscle strength and endurance measured as mean change from admission to discharge and from discharge to 3 months after discharge, with comparisons between groups. Systemic inflammation measured as mean change from admission to discharge and from discharge to 3 months after discharge, with comparisons between groups. Accelerometer-based physical activity level measured at admission as mean change from admission to the week after discharge, with comparisons between groups.

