### Study hypotheses and aims

We hypothesize that standard usual care combined with daily supervised in-bed cycling or standard usual care combined with booklet exercises is superior to standard usual care alone in reducing length of hospital stay, reducing the risk of 90-day readmission, and 180-day mortality, counteracting loss of muscle mass, muscle strength, functional ability, low/reduced health-related quality of life, increase in fat mass, reducing systemic inflammation, and increasing the physical activity level after discharge.

The primary aim of the study is to determine if supervised in-bed cycling or supervised booklet exercises during hospitalization with CAP reduces length of hospital stay. Secondary aims are to determine if supervised in-bed cycling or supervised booklet exercises during hospitalization with CAP improves prognosis (e.g., reduces the risk of readmission and mortality) and minimizes/counteracts hospital-related changes in body composition, muscle strength, functional ability, health-related quality of life, systemic inflammation, and physical activity level after discharge. Additional aims are to investigate if supervised in-bed cycling or supervised booklet exercises during hospitalization with CAP improves glucose metabolism, diabetes and health status, and frailty.

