**Fig. 4 Fig4:**
[figure not shown]
SPIRIT standard protocol items with time schedule of enrolment, interventions and assessments. *BIA* bioelectrical impedance analysis, *DXA* dual-energy X-ray absorptiometry, *ECG* electrocardiogram, *EQ-5D-5L* health-related quality of life, *HbA1c* hemoglobin A1c, *IPAQ* International Physical Activity Questionnaire, *OGTT* oral glucose tolerance test. Asterisk indicates standard usual care. Superscript digit 1 indicates the following: After radiological diagnose of pulmonary infiltrate on chest X-ray/CT in combination with at least one symptom of lower respiratory tract infection at admission, eligibility will be assessed, and potential participants will be approached. Superscript digit 2 indicates the following: The physical training is a supervised exercise program with one session per day. Superscript digit 3 indicates the following: Basic blood samples will be drawn daily as part of routine tests during hospitalization and analyzed for hematologic, renal, endocrine, cardiac, and hepatologic markers. Blood samples stored in the biobank will be analyzed for markers of inflammation. Superscript digit 4 indicates the following: Readmission up to 3 months after discharge. Superscript digit 5 indicates the following: mortality during admission and up to 6 months after discharge. The table is adapted from the SPIRIT recommendations [25]

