## Outcomes and timing of assessments

The attending physician will evaluate whether the patient is ready for discharge. Readiness for discharge is based on the modified Halm’s criteria for clinical stability in CAP [26]. Once the criteria are met, the different measurements scheduled for discharge will be performed. The different outcome variables and timing of assessments are listed in Table 2.

**Table 2 Tab2:** Outcome

Outcome domain	Specific measurement	Specific metric				Methods of aggregation			Time point
		Value at a time point	Change from baseline	End value	Time to event	Mean	Percent/proportion	Absolute number	
Length of hospital stay	Discharge date–admission date			x		x			Discharge
Readmission	Readmission date–discharge date				x		x	x	3 months
Mortality	Mortality date–discharge date				x		x	x	6 months
Total lean mass	DXA scan		x			x			Discharge
Total fat mass	DXA scan		x			x			Discharge
Total fat-free mass	BIA scan		x			x			Discharge
Leg lean mass	DXA scan		x			x			Discharge
Trunk fat mass	DXA scan		x			x			Discharge
Health-related quality of life	EQ-5D-5L		x			x			Discharge
Activities of daily living	Barthel Index-100		x			x			Discharge
Muscle strength	Hand grip strength		x			x			Discharge
Muscle endurance	30-s chair stand test		x			x			Discharge
Systemic inflammation	Plasma samples		x			x			Discharge
Physical activity	AX3 accelerometers		x			x			After discharge
Glucose metabolism	Oral glucose tolerance test		x			x			3 months
Diabetes status	HbA1c	x					x	x	3 months
Prior physical activity level	IPAQ questionnaire	x					x	x	3 months
Frailty	Frail scale questionnaire	x					x	x	3 months

*BIA* bioelectrical impedance analysis, *DXA* dual-energy x-ray absorptiometry, *EQ-5D-5L* health-related quality of life, *HbA1c* hemoglobin 1Ac, *IPQA* International Physical Activity Questionnaire

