### Pre-planned analysis

Available-case analyses will be carried as the main aim is to evaluate the efficacy of the interventions. This means that patients will contribute to the statistical analyses until they drop-out or the study is terminated. Also, as patient drop-out in most cases will be caused by factors, which will happen independently of this study, missing at random will most likely be an acceptable assumption. Additionally, subgroup analyses for patients without COVID-19 CAP will be carried out as patients with COVID-19 CAP may stay longer at the hospital.

For the primary outcome (length of hospital stay), analysis of covariance will be performed to quantify differences between groups. The following covariates will be included in the model: age, gender, CURB-65 score, BMI, and total number of comorbidities (categories 0, 1, 2, > 2). The estimated mean difference (in changes) between the standard usual care group and the two exercise groups (standard usual care vs. exercise booklet and standard usual care vs. in-bed cycling) with the corresponding adjusted confidence interval (CI) and *p* values will be reported. Both CIs and *p* values will be adjusted utilizing correlations between estimates and tests in a less conservative way compared to Bonferroni adjustment [36].

Survival analysis with Kaplan-Meier estimation and Cox proportional hazards regression will be performed to explore differences between groups in time to readmission. Hazard ratios comparing the standard usual care group with the two exercise groups (standard usual care vs. exercise booklet and standard usual care vs. in-bed cycling) will be estimated and reported together with corresponding CIs and *p* values. Kaplan-Meier estimation and Cox proportional hazards regression will be performed to explore differences between groups in time to mortality. Hazard ratios comparing the standard usual care group with the two exercise groups (standard usual care vs. exercise booklet and standard usual care vs. in-bed cycling) will be estimated and reported together with corresponding CIs and *p* values. For readmission, data will be censored 3 months after discharge, while for mortality, censoring will occur 6 months after discharge.

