### Randomization: sequence generation and allocation concealment

Patients are randomly assigned (1:1:1) in permuted blocks according to computer-generated random numbers (R version 3.4.1), to undergo either standard usual care or booklet exercise or in-bed cycling. The randomization is performed at the day of inclusion (within 24 h of admission) after patients have provided informed consent to participate (additional file 2). No stratification factors are used in the randomization algorithm. The randomized sequence is generated centrally by a researcher not involved in the testing. The allocation is delivered to the researcher responsible for the exercise interventions in sealed envelopes at the time of inclusion. Patients are informed about their allocation after baseline assessment (at days 0 or 1) has been completed. The researcher performing the baseline assessment is responsible for informing the patients about their allocation. The study allocation is blinded for the nurses, physiotherapists, and clinicians treating the patients; however, the researcher responsible for the exercise intervention and outcome assessor is unblinded. Even though blinding could limit the occurrence of bias when collecting and assessing data, the researchers involved in this study has no influence on treatment plans or evaluation of readiness for discharge. The risk of bias due to lack of blinding is therefore evaluated to be relatively low.

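### The mortality clock starts at discharge, so the 180-day mortality comparison is conditional on leaving hospital alive and gives deaths during the admission no valid survival time

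*Protocol article*

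**What the plan says.** Three places in the protocol article tie the mortality outcome to discharge, and they agree with each other:

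- Secondary outcomes: "readmission and mortality measured as time to event within 3 and 6 months from discharge".
- Table 2 (Outcomes and timing of assessments): the mortality row gives "Mortality date–discharge date" as the measurement and marks it as time to event, with a proportion and an absolute number as summaries.
- Pre-planned analysis: "Kaplan-Meier estimation and Cox proportional hazards regression will be performed to explore differences between groups in time to mortality", and "for mortality, censoring will occur 6 months after discharge".

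Three other places do not fit that origin:

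- Study hypotheses and aims: superiority is hypothesised in "reducing the risk of 90-day readmission, and 180-day mortality", with no restriction to patients who leave hospital alive. The Abstract also lists 180-day mortality without restriction.
- Fig. 4 legend, note 5: the schedule covers "mortality during admission and up to 6 months after discharge". Note 4, on readmission, mentions only the period after discharge.
- Randomization: allocation takes place on the day of inclusion, no later than 24 hours after admission.

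No section says how a death before discharge enters the survival analysis.

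**The concern.** A randomised comparison of survival is protected by randomisation only if follow-up starts at randomisation, or at a point that allocation cannot influence. Discharge is not such a point. It comes after randomisation, and the primary aim is to bring it forward. A clock that starts there compares those who survived to discharge in each arm, and these groups need not be alike even when the randomised groups are.

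Two things are at stake. First, an effect of training on deaths during the admission, when all the supervised sessions take place, would not show in the hazard ratio in either direction. Second, if training alters who survives to discharge, the hazard ratio after discharge can move although total mortality does not. If training only postponed some ward deaths until after discharge, the training arms would look worse.

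**Working it through.** **The plan's own figure.** The only sample-size figure concerns length of stay. From Statistical power and sample size calculations: difference 2 days, SD 3.5 days, two-sided alpha 0.025, power 0.8, drop-out 15%. Per group n = 2 × (2.241 + 0.842)² × 3.5² / 2² = 58.2, so 59. Then 59 / 0.85 = 69.4, so 70, and 3 × 70 = 210. The figure reproduces and does not depend on the mortality definition. No event count or power is stated for mortality.

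**What the definition does with a ward death.** Survival time is death date minus discharge date. For a patient who dies before discharge there is no such interval. If the date of death is entered as the discharge date, the time is zero for every such patient, whichever day they died. Either way the time from randomisation to death is lost. The proportion and count columns sit in the same discharge-based row of Table 2, so they do not clearly bring these deaths back.

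**How many deaths could be involved (illustration).** The Background gives 14% overall mortality in patients hospitalised with CAP, without a time horizon. 0.14 × 210 = 29.4 deaths, or 9.8 per arm. The in-hospital share is not given, so a range is assumed. The last column is 1/√(1 − share), the factor by which the standard error of the log hazard ratio grows when those events are lost.

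| Assumed in-hospital share | Deaths before the clock starts | Deaths counted | SE factor |
|---|---|---|---|
| 10% | 2.9 | 26.5 | 1.05 |
| 25% | 7.4 | 22.1 | 1.15 |
| 50% | 14.7 | 14.7 | 1.41 |
| 60% | 17.6 | 11.8 | 1.58 |

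**Which way the estimate can move (illustration).** Take 14% total mortality in the control arm and compare two risk ratios: all deaths over all randomised, and deaths after discharge over patients discharged alive.

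*Training halves in-hospital deaths and does nothing afterwards.*
- Share 50%: control 0.07 in hospital and 0.07 after; training 0.035 and 0.07. All deaths: 0.105 / 0.14 = 0.75. Discharge clock: (0.07 / 0.965) / (0.07 / 0.93) = 0.96.
- Share 25%: all deaths 0.1225 / 0.14 = 0.875. Discharge clock: (0.105 / 0.9825) / (0.105 / 0.965) = 0.98.

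*Training only postpones half of the in-hospital deaths until after discharge.*
- Share 50%: all deaths (0.035 + 0.105) / 0.14 = 1.00. Discharge clock: (0.105 / 0.965) / (0.07 / 0.93) = 1.45.
- Share 25%: all deaths 1.00. Discharge clock: (0.1225 / 0.9825) / (0.105 / 0.965) = 1.15.

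The shares and effects are assumptions. They show that a real benefit can nearly vanish and that an apparent harm can arise from none.

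**The case against.** Several points on the other side have weight.

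- A reader might infer that the plan excludes in-hospital deaths. It nowhere says so; their loss follows from the formula in Table 2. A reader might also call them invisible, but the Fig. 4 legend has them recorded, and the Safety section requires serious adverse events to be reported. Both stronger readings fail. What stands is that the planned survival analysis has no place for these deaths.
- A reader might see a flat contradiction between Fig. 4 and the outcome definition. Fig. 4 is a schedule of what is recorded, and a trial may record more than one analysis uses. It is better called a mismatch. The mismatch with the unrestricted 180-day hypothesis remains.
- A reader might say that the intervention exists only in hospital. Supervised training does, but both exercise arms go home with the booklet, a training diary and encouragement to stay active (Training diary and exercise booklet). Mortality after discharge is therefore a fair question, but a conditional one.
- The 14% is a background figure. The eligibility criteria exclude patients who cannot consent, cannot move their legs, are immunosuppressed, or are terminally ill with active treatment stopped within 48 hours. In-hospital deaths may therefore be few.
- Mortality is a secondary outcome that the plan sets out to explore, and power is low with either clock. With 9.8 deaths per arm the standard error of a pairwise log hazard ratio is about √(2 / 9.8) = 0.45, and 80% power at two-sided 0.05 would need a hazard ratio near exp(−2.80 × 0.45) = 0.28.
- An article may leave detail to the full protocol. Here, however, the origin, the formula and the censoring point are all stated, so the problem lies in what is fixed and not in what is left out.

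**Conclusion.** The concern holds as a flaw in a stated definition. The mortality comparison starts at a post-randomisation event whose timing the intervention aims to change, it does not match the unrestricted 180-day hypothesis, and it gives deaths before discharge no valid survival time. It can miss or distort an effect on deaths during supervised training.

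Its size in this trial cannot be derived from the document. The range of about 3 to 18 deaths out of about 29 rests on applying the background 14% to 210 patients and on an assumed in-hospital share of 10% to 60%; the eligibility criteria may put the true number at or below the low end. The risk ratios are likewise illustrations.

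A reader might infer that the trial's main result is at risk. The documents do not support that for this point: mortality is secondary, and the sample size of 210 rests on length of stay alone. The correction is nevertheless worth making, because it is cheap and the present definition does not answer the stated question.

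**What to change.** Define the secondary mortality outcome as time from randomisation to death from any cause, include deaths during the index admission, and censor at 180 days after randomisation. Change the mortality row of Table 2, the mortality sentence under Secondary outcomes, and the censoring rule under Pre-planned analysis, so that all three agree with the hypothesis and with the Fig. 4 legend. If mortality after discharge is still of interest, report it as a supplementary description labelled as conditional on discharge alive.

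No new data are needed. Deaths are already recorded during admission and up to 6 months after discharge, and that period extends past 180 days from randomisation because discharge follows randomisation. The cost is a documented amendment to a secondary outcome in an open-label trial that is already recruiting, communicated to registries and committees as the Trial status section requires. It should be dated before any between-group analysis. The primary outcome and the sample size do not change.

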**Methods:**

This study is a randomized controlled trial with three parallel experimental arms. Based on a sample size calculation, a total of 210 patients admitted with CAP at Nordsjællands Hospital, Hillerød, Denmark, will be recruited. Patients will be randomly allocated (1:1:1) to either (1) standard usual care, (2) standard usual care combined with in-bed cycling, or (3) standard usual care combined with exercises from a booklet. The primary outcome is differences in length of hospital stay between groups, with secondary outcomes being differences between groups in time to (1) 90-day readmission and (2) 180-day mortality. Further secondary outcomes are differences in changes from baseline between groups in (3) lean mass, (4) fat mass, (5) fat-free mass, (6) physical capacity, (7) health-related quality of life, (8) systemic inflammation, and (9) physical activity level after discharge. Data on length of hospital stay, readmission, and mortality will be collected from patient files, while total lean, fat, and fat-free mass will be quantitated by dual-energy x-ray absorptiometry and bioelectrical impedance analysis. Physical function will be assessed using grip strength, 30-s chair stand tests, and Barthel Index-100. Health-related quality of life will be assessed with the EQ-5D-5L questionnaire. Systemic inflammation will be assessed in blood samples, while accelerometers are used for measuring physical activity.

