For secondary outcomes (total lean mass, total fat mass, total fat-free mass, leg lean mass, trunk fat mass, EQ-5D-5L score, Barthel Index-100 score, grip strength, 30-s CST, systemic inflammation, and physical activity [AX3]), linear mixed models with treatment by time interaction as a fixed-effects term and patient-specific random intercepts will be fitted to explore differences in changes from baseline between groups. Specifically, the estimated mean difference (in changes) between the standard usual care group and the two exercise groups (standard usual care vs. exercise booklet and standard usual care vs. in-bed cycling) with corresponding CIs and *p* values will be reported. Logarithm transformations will be applied where appropriate (to handle right-skewed distributions), and resulting estimates and CIs will be back-transformed accordingly.

Likewise, for exploratory outcomes (glucose metabolism), linear mixed models with treatment by time interaction as a fixed-effects term and patient-specific random intercepts will be fitted to explore differences in changes from baseline between groups. Specifically, the estimated mean difference (in changes) between the standard usual care group and the two exercise groups (standard usual care vs. exercise booklet and standard usual care vs. in-bed cycling) with corresponding CIs and *p* values will be reported.

For other categorical outcomes (IPAQ score, diabetes status, and frailty score), differences between groups at 3 months will be explored by the chi-squared test (r × c tables) and expressed as counts and percentages, and *p* values will be reported. In all statistical analyses, *p* values < 0.05 will be considered significant.

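### Secondary outcomes: the 3-month comparison is defined as change from discharge, a value the training is meant to alter, and this conflicts with the change from baseline stated elsewhere

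*Protocol article*

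**What the plan says.** The Secondary outcomes section defines two successive changes for the five body-composition measures: "measured as mean changes from admission to discharge and from discharge to 3 months after discharge, with comparisons between groups". The same pattern is used for quality of life and activities of daily living, for inflammation, and for strength: "Muscle strength and endurance measured as mean change from admission to discharge and from discharge to 3 months after discharge". That makes ten outcomes. The section defines no admission-to-3-month change for any of them.

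Other parts of the article use a different reference:

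- **Abstract, Methods:** "Further secondary outcomes are differences in changes from baseline between groups in (3) lean mass", followed by the other measures.
- **Pre-planned analysis:** for these same outcomes, linear mixed models with a treatment-by-time term "will be fitted to explore differences in changes from baseline between groups". No time points are named.
- **Table 2:** ticks the change-from-baseline column for these outcomes, but gives discharge as their only time point.
- **Measurement of outcome variables:** places baseline testing at days 0 or 1.
- **Other outcomes:** takes the 3-month change in glucose metabolism from admission.

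Study hypotheses and aims describes training given in hospital and asks whether it "minimizes/counteracts hospital-related changes in body composition, muscle strength, functional ability, health-related quality of life, systemic inflammation, and physical activity level after discharge". The Primary outcome section adds: "The primary outcome is length of hospital stay from the time of admission until discharge".

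**The concern.** A change score compares randomised arms fairly when its starting value was measured before treatment could act. Discharge does not meet that condition. The supervised sessions have been given by then, and the stated aim is that they shift these very measures by that point. If training shortens the stay, the reference value is also taken at a different time in each arm.

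An arm that lost less muscle or function in hospital has less to regain. Its gain after discharge can be smaller even when its patients are no worse off, or are better off, at 3 months. The question a reader brings to a 3-month result is whether trained patients are then better off. As the Secondary outcomes section is worded, no defined contrast answers it. Because the Pre-planned analysis section treats p below 0.05 as significant in every analysis, a negative second-period contrast could be reported as significant harm.

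**Working it through.** **The plan's own figure.** The article gives no effect size, standard deviation or correlation for any secondary outcome. Its only sizing is for length of stay: a 2-day difference, SD 3.5 days, two-sided 0.025, power above 0.8, 15% drop-out. This reproduces: 59 per arm evaluable, 59/0.85 = 69.4, so 70 per arm and 210 in total. The 59 per arm is reused below.

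**The identity.** Let d be the arm difference at discharge and r the share of it remaining at 3 months. Randomisation makes the expected difference at admission zero.

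- Admission to discharge: d
- Admission to 3 months: r·d
- Discharge to 3 months: r·d − d = (r − 1)·d

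So r = 1 gives 0, r = 0.5 gives −0.5d, and r = 0 gives −d. For fat mass and inflammation a benefit is a lower value, so the signs reverse and the logic is the same.

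**Numerical illustration (assumed values).** Usual care loses 1.0 kg of lean mass in hospital, training loses 0.5 kg, and both stand 0.2 kg below admission at 3 months. From discharge, usual care gains 0.8 kg and training 0.3 kg, a contrast of −0.5 kg. From admission, the contrast is −0.2 − (−0.2) = 0.

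**Check in the planned type of model.** Data were simulated for 4,000 patients in two arms and fitted with a random-intercept model with treatment-by-time terms (true d = 0.5, patient variance 0.7, residual variance 0.3).

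| Share kept at 3 months | 3-month term, baseline as reference | 3-month term, discharge as reference |
|---|---|---|
| All | 0.504 | −0.002 |
| Half | 0.250 | −0.237 |
| None | 0.005 | −0.478 |

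The same fitted model yields both columns. Only the reference visit differs.

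**How often this would matter.** All inputs here are assumptions, with unit variance at each visit and a two-sided 0.05 test.

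*Set A: d = 0.5 SD, 59 per arm, a common between-visit correlation ρ.* The standard error of a contrast is √(2(1 − ρ))·√(2/59). At ρ = 0.7 it is 0.775 × 0.184 = 0.143. With nothing kept, the probability of significance against training is Φ(0.5/0.143 − 1.96) = 0.94. With half kept it is Φ(0.25/0.143 − 1.96) = 0.42.

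*Set B: an in-hospital effect sized for 80% power on admission to discharge, correlation 0.8 between those visits and 0.5 between each of them and 3 months.* In units of √(2/n), d = 2.80 × √0.4 = 1.77, and the standard error of the discharge-to-3-month contrast is √(2 × 0.5) = 1. With nothing kept, Φ(1.77 − 1.96) = 0.425. With half kept, Φ(0.885 − 1.96) = 0.141.

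| Discharge-to-3-month contrast significant against training | Set A, ρ = 0.5 | Set A, ρ = 0.7 | Set A, ρ = 0.8 | Set B |
|---|---|---|---|---|
| None kept | 0.78 | 0.94 | 0.99 | 0.43 |
| Half kept | 0.27 | 0.42 | 0.57 | 0.14 |
| All kept | 0.025 | 0.025 | 0.025 | 0.025 |

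When the benefit is kept in full, the discharge-based contrast favours training significantly only at the 0.025 chance rate. The admission-to-3-month contrast does so with probability 0.78, 0.94 and 0.99 in Set A and 0.43 in Set B. Set A's equal correlations match what a random-intercept model implies; Set B's unequal ones do not.

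**The case against.** The strongest defence is that the analysis section, the abstract and Table 2 all refer to baseline. If the mixed model is reported as the analysis section words it, the 3-month estimate is already the sound one and nothing reaches the results. This stands as a limit on the point. It does not remove it: the analysis section names no time points, Table 2 lists only discharge, and the one explicit 3-month definition uses discharge. A separate analysis plan might settle the matter, but the complaint concerns a definition the article does state.

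Second, the two changes are given as a pair, and their point estimates add up to the admission-to-3-month difference. The first has a proper reference and matches the aim of countering in-hospital decline. That is fair, but no estimate, confidence interval or p value is defined for the sum.

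Third, the section on the training diary says the exercise arms leave hospital with the booklet, a diary and advice to stay active. The course after discharge is therefore of some interest in itself. This also stands, although the contrast mixes any effect of that component with fading of the in-hospital effect.

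A reader might infer more: that the trial will report false harm, or that the outcome always looks worse the better training works. The documents support neither. The first depends on which wording governs and on inputs the article does not give. The second needs at least partial fading: full persistence gives zero, and further gain after discharge gives a positive contrast. Nor can any single probability above be called the trial's risk.

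**Conclusion.** The point holds as a badly fixed outcome definition together with an internal contradiction. The identity is exact and needs no assumption beyond randomisation: followed as written, the Secondary outcomes section returns zero for a lasting benefit and an adverse difference for a faded one. The probabilities are illustrations only. With complete fading they run from about 0.4 to over 0.9, depending on assumed effect size and correlations.

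Severity is should-fix. Ten secondary outcomes are affected, and their analysis is worded as exploring differences. Length of stay, the sample size, readmission, mortality and accelerometer activity are untouched.

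**What to change.** In the Secondary outcomes section, define the 3-month outcomes for the ten listed measures as change from the admission baseline (days 0 or 1) to 3 months after discharge, and keep the admission-to-discharge change as it is. In Pre-planned analysis, name the time points and state that the 3-month result is the treatment-by-time contrast with the admission baseline as reference, reported with its confidence interval and p value for each exercise arm against usual care. In Table 2, add 3 months beside discharge as a time point for these outcomes.

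The discharge-to-3-month change may stay as a supplementary description of the post-discharge course. It should not serve as the test of whether trained patients are better off at 3 months.

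The cost is wording only: the same visits, data and mixed model. There is a side benefit for the four DXA outcomes. Anthropometry and body composition lists scans at days 0 or 1, day 5, and 1 and 3 months but none at discharge, whereas Measurement of outcome variables says the baseline tests are repeated at discharge. An admission reference removes the 3-month result's dependence on that scan.
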